### Clinical effectiveness in a real-world setting

To assess the clinical effectiveness of blinatumomab adapted to LMIC contexts, the research team will assess the quality of administration and examine patient outcomes. To assess the quality, a standardized documentation tool was designed to record infusion interruptions and track the frequency and severity of AEs related to blinatumomab with a focus on AEs observed in HIC (as defined by Common Terminology Criteria for Adverse Events [CTCAE] v5.0) [33]. These will be completed by treating physicians and bedside nurses and analyzed at St. Jude. To assess the patient outcomes, the local site physicians will collect deidentified clinical data. These secondary data are available as part of routine clinical care and include patient enrollment criteria, AE frequency and severity, and clinical outcomes including ALL disease status after cycles 1 and 2 of blinatumomab, duration of each cycle, and short- and long-term patient outcomes that include relapse, subsequent management including bone marrow transplant, and mortality at 12 months after administration. This information will serve as a surrogate clinical measure as part of the summative evaluation to determine the adequacy of training programs and identify the domains for implementation program adaptation (e.g., patient suitability criteria, administration method, and supportive care) to improve utilization in current and future sites. Clinical data will be entered into the REDCap database by local physicians who have completed Collaborative Institutional Training Initiative (CITI) training and a Data Abstraction training module on Cure4Kids.

### Process evaluation

We will perform a process evaluation using the Reach, Effectiveness, Adoption, Implementation, and Maintenance (RE-AIM) framework to characterize the reach, adoption, and implementation of the BHAP program [34]. This will include analysis of training participation, user engagement and utilization of online training materials, and breadth of patient selection.

### Aim 3: Prepare an implementation roadmap reflecting important determinants of implementation success and implementation strategies to support the translation of blinatumomab into future LMICs.

In aim 3, the results from analyses for aims 1 and 2 will be compiled to fully characterize the relevant contextual barriers, key implementation strategies, implementation outcomes, and areas of adaptation vs fidelity to facilitate the successful implementation of blinatumomab (Table 6).

**Table 6 Tab6:** Data use to address specific research questions. Key research questions in the INOVATION program mapped to specific measurement tools used to address each question

Research question	Data source
*(1) Can blinatumomab be adapted for LMIC settings, and is it feasible, acceptable, and appropriate?*	1) Implementation outcomes assessments (FIM, AIM, IAM, cost) 2) Semi-structured interviews 3) Program evaluation group interview
*(2) Does an adapted multidisciplinary training program improve these implementation outcomes?*	1) Knowledge assessments 2) Implementation outcomes assessments (FIM, AIM, IAM, cost)
*(3) Are there contextual factors (readiness, capacity, perceived complexity) that correlate with successful implementation?*	1) Hospital assessment questionnaire 2) Barrier assessments: complexity assessment, ICS, ORIC 3) Implementation outcomes assessments (FIM, AIM, IAM) 4) Semi-structured interviews
*(4) What are the key strategies as perceived by stakeholder groups and are these the same between different groups?*	1) Implementation strategy feedback 2) Program evaluation group interview
*(5) What is stakeholder satisfaction with this implementation-guided approach?*	1) Semi-structured interviews with implementation teams 2) Program evaluation group interview
*(6) Is the effectiveness of this adapted administration of blinatumomab the same as what has been documented in high-income settings?*	1) Patient enrollment information 2) Patient safety record: adverse event reporting 3) Management records: interruption record 4) Clinical outcome data

*LMICs* Low- and middle-income countries, *FIM* Feasibility of Intervention Measure, *AIM* Acceptability of Intervention Measure, *IAM* Intervention Appropriateness Measure, *ICS* Implementation Climate Scale, *ORIC* Organizational Readiness for Implementing Change

The research team will assemble an informed implementation process model, “Implementation Roadmap” that reflects the core domains and modifiable variables based on the unique context, characteristics of the intervention, and stakeholder values. This model will contain “standard elements” generalizable to all centers, which include a phased strategy plan, readiness assessment, training materials, workflow documents, an assessment package to monitor implementation, budget impact models, and tools to support local adaptation processes. It will also include additional variables or strategies that can be included based on the unique needs and resources of the institution. Version 1.0 of this model will be informed from the three pilot institutions and then undergo a review by a focus group and stakeholder qualitative survey and then serve as a mechanism to scale-out access to blinatumomab. With each iteration of implementation at new institutions, new findings from the evaluation process will be incorporated to further refine the model to improve its utility and generalizability to a wider variety of resource settings.

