### Phase 2: Baseline data collection and program planning

The BHAP Core Team, comprised of multidisciplinary representatives from St. Jude and AMGEN, reviewed and assimilated the institutional administration guidelines, prescribing information, and relevant literature from HICs institutions [15–18] and identified the key administration and management issues for blinatumomab. This helped identify the core domains (indication, dose, and duration) of blinatumomab delivery. The BHAP core team designed a questionnaire to characterize the baseline capacity at LMIC sites, including hospital funding, clinical infrastructure, intensive care ward capacity, nursing care, eligible patient population, standardized operating procedures, medication procurement procedures, advanced treatment experience, and training needs for physicians, nurses, and pharmacists. The 64-question survey was reviewed for content, cultural variations, and ease of use by multidisciplinary international experts. One local physician at three LMIC pilot centers completed the survey, and responses were supplemented through informal discussion with the BHAP core team. The modifiable elements from these preliminary investigations traced back to two CFIR domains, the inner setting (e.g., implementation climate, culture, readiness) and the intervention characteristics (e.g., complexity, adaptability, cost, relative advantage), which are consistent with the findings from a systematic review by Means et al. demonstrating inner setting and intervention characteristics were the most utilized CFIR domains in LMIC settings [22]. Based on BHAP Core Team consensus, recommended best practices for blinatumomab administration were preemptively adapted to include reduced frequency laboratory monitoring, inpatient-only administration, AE management, and standardized bag change schedule. With complex interventions, we expect additional barriers to emerge during implementation and will assess the needs for further adaption based on experience with pilot sites.

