### Methods

This convergent, mixed methods study addresses stated research questions based on the CFIR framework. Table 2 lists data sources. Qualitative methods include open-ended questions, stakeholder interviews, and meeting notes. Quantitative methods include surveys and secondary clinical and costing data. Methods will define the barriers and facilitators and explore the impact of these barriers and strategies on implementation outcomes, including feasibility, acceptability, appropriateness, and clinical effectiveness of blinatumomab in resource-limited settings using an effectiveness-implementation hybrid type 2 case series design. Due to ethical implications and prioritization of patient safety in these centers, randomization is not possible.

**Table 2 Tab2:** Study data sources including data collector, data collection method, correlation to specific CFIR domain, and target study participant. Matrix of data collection methods

Type of data	Data collectors	Data collection method	CFIR domain	Study participants
Primary data	BHAP core team	Hospital assessment questionnaire	Inner setting	Pilot center physician champion
	St. Jude research team	Provider knowledge assessment	Inner setting	Multidisciplinary pilot center providers
		Organization Readiness for Implementing Change (ORIC)	Intervention characteristics	Pilot center implementation team
		Implementation Climate Scale (ICS)	Inner setting	Pilot center implementation team
		Complexity of intervention assessment	Intervention characteristics	Pilot center implementation team
		Implementation outcome surveys (Feasibility of Intervention Measure, Acceptability of Intervention Measure, Intervention Appropriateness Measure)	Intervention characteristics	Pilot center implementation team
		Strategy ranking survey	Process	Pilot center implementation team
		Stakeholder interviews (barrier assessment, informed adaptation of patient eligibility criteria and training materials, strategy prioritization, and assessment)	Inner setting Process Intervention characteristics Outer setting	Key stakeholders
		Meeting notes	Process	Key stakeholders
		Group interview (strategy analysis, feedback on training strategy, implementation outcome, team dynamics, identifying unanticipated challenges, and adaptation of implementation, provider satisfaction)	Inner setting Process Intervention characteristics	Pilot center implementation team

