Secondary data	Local site providers	Medication interruption record	Intervention characteristics	Blinatumomab recipients
	Local site providers	Adverse event reporting, severity, and number of events	Intervention characteristics	Blinatumomab recipients
	Local site providers	Disease outcomes (MRD status, remission status, proceed to transplant, mortality)	Intervention characteristics	Blinatumomab recipients
	Local site providers	Participant satisfaction	Intervention characteristics	Patient and family
	Local site providers	Baseline patient characteristics	Intervention characteristics Inner setting	Blinatumomab recipients
	Local site providers	Delivery cost of blinatumomab	Intervention characteristic	Blinatumomab recipients
Process indicators	St. Jude research team	Attendance of training sessions, utilization of web-based resources, and proportion of patients enrolled in the BHAP program	Process	Pilot center providers

*BHAP* Blincyto® Humanitarian Access Program, *CFIR* Consolidated Framework for Implementation Research, *MRD* Minimal residual disease

The results will yield an in-depth understanding of key determinants and prioritization of key implementation strategies, which will be assembled into a framework to facilitate real-world scalability of blinatumomab in future centers.

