*LMICs* Low- and middle-income countries, *BHAP* Blincyto® Humanitarian Access Program, *QUAN* Quantitative, *QUAL* Qualitative

We selected well-established measurement tools that have been validated in HICs and were chosen because they are pragmatic, reviewed and agreed upon by stakeholders, and when compiled have less than 50 questions that can be completed in less than 30 min. The quantitative surveys to assess barriers include the Implementation Climate Scale (ICS) [24], Organizational Readiness for Implementing Change (ORIC) [25], and a complexity assessment. Implementation outcome survey assessments include Acceptability of Intervention Measure (AIM), Intervention Appropriateness Measure (IAM), and Feasibility of Intervention Measure (FIM) [26]. These measures of implementation outcomes were selected for their salience with stakeholders and because they are considered “leading indicators” of implementation success for early-stage initiatives [26]. Survey data collected online through Qualtrics will be housed at the Department of Global Pediatric Medicine at St. Jude.

The research team will conduct two semi-structured group interviews with the implementation team to collect additional insights into the site-specific determinants. Interview #1 will be done 3 months after training and after the site has started administering blinatumomab. The CFIR Interview Development Tool will guide the development of the interview guide and will be adapted based on experience with the pilot sites [27]. The team will ask open-ended questions about the implementation processes, barriers, and facilitators and will elicit feedback on the training program. Interview #2 will be done 1 year after training, wherein the research team will ask open-ended questions on site-specific fidelity vs adaptations to recommended administration guidelines, strategies, emerging determinants, costs, team dynamics, adequacy of training program, utility of standardized documentation tools, and parent perception of treatment.

Interviews will be audio-recorded and transcribed verbatim, and the team will use thematic coding methods to analyze and interpret the results. Written transcripts will be reviewed independently by two research team members to identify emergent themes to build a codebook. Then, each transcript will be reviewed again using the codebook. The thematic coding process will focus on process improvement.

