Descriptive statistics will be used to characterize the barriers and facilitators to blinatumomab implementation in LMICs. This will include describing core components of implementation, such as site infrastructure, climate, readiness, and intervention complexity. The survey will be summarized by frequency tables and cross-tabulation to study any associations. The chi-squared and Fisher’s exact test will be used to assess the associations. Comparisons will be made with assessments of barriers done over time (pre-training; 3, 6, and 12 months post-training). Univariate and multivariable logistic regression analysis will be used, as appropriate, to study the correlations among scores of clinical infrastructure, readiness, climate, and intervention complexity with implementation outcomes (feasibility, acceptability, and appropriateness) within and across institutions. Collectively, this information will be used to understand barriers and site-specific adaptations to modify the strategy approach and training program for medication delivery.

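### For research question 3, the only scored measure of successful implementation is rated by the same team, at the same waves, as the readiness, climate and complexity scores it is correlated with

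*Protocol article*

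**What the plan says.** All references are to the protocol article.

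- **Table 6 (Aim 3).** For the question "Are there contextual factors (readiness, capacity, perceived complexity) that correlate with successful implementation" the sources are the hospital assessment questionnaire, then "2) Barrier assessments: complexity assessment, ICS, ORIC", then "3) Implementation outcomes assessments (FIM, AIM, IAM) 4) Semi-structured interviews".
- **Aim 1, analysis paragraph.** Univariate and multivariable logistic regression will relate scores for infrastructure, readiness, climate and "intervention complexity with implementation outcomes (feasibility, acceptability, and appropriateness) within and across institutions".
- **Table 4 and Table 2.** Complexity, ICS, ORIC, AIM, IAM and FIM all go to the implementation team: before training, then at 3, 6 and 12 months. In Table 2 the row "Implementation outcome surveys (Feasibility of Intervention Measure, Acceptability of Intervention Measure, Intervention Appropriateness Measure" names the same respondents. The hospital questionnaire is different: the physician champion completes it once, before enrollment in the drug donation program.
- **Aim 1, choice of measures.** FIM, AIM and IAM are described as leading indicators of "implementation success for early-stage initiatives". The barrier and outcome scales are compiled into one package of under 50 questions.
- **Methods, opening paragraph.** Here the outcomes on which barriers may act include clinical effectiveness as well as feasibility, acceptability and appropriateness.
- **Table 2, other data.** The study also collects the "Medication interruption record", adverse events, disease outcomes, training attendance, web use and the proportion of patients enrolled. Table 6 lists the first three for question 6 only and the last three for no question.
- **Domain of readiness.** Table 2 files ORIC under intervention characteristics. The Phase 2 section places readiness in the "inner setting (e.g., implementation climate, culture, readiness".

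**The concern.** When one person rates both the predictor and the outcome in one sitting, any general tendency of that person enters both scores. Someone well disposed to the program will tend to rate the hospital as readier, the drug as less complex, and its use as more feasible and acceptable. That produces a correlation even if readiness has no bearing on how well the drug is delivered. The raters are also people whom the site lead selects for having led the implementation, so they are rating their own effort.

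The answer to question 3 is one input to the Implementation Roadmap, which is meant to identify determinants of implementation success for future sites. If the quantitative result is presented as a link with success, readers may take it as evidence about delivery when it is evidence about agreement among opinions. The study holds records that speak to delivery, but the plan for this question does not use them.

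**Working it through.** **1. Respondent, timing and type of each quantitative input to question 3 (Tables 2, 4 and 6)**

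| Input | Role | Respondent | Timing |
|---|---|---|---|
| ORIC, ICS, complexity | contextual factor | implementation team | four waves |
| FIM, AIM, IAM | outcome | implementation team | same four waves |
| Hospital questionnaire (capacity) | contextual factor | physician champion | once, before enrollment |

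All three scored outcomes are perceptions by the team that also rates readiness, climate and complexity. At the three pilot sites the Aim 1 text puts the implementation assessments 1 year after training, so barriers and outcomes are rated together there too. Capacity has a separate source and time.

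**2. What a shared rater tendency does**

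The plan gives no figure to reproduce here. Assume that a share *m* of each score's variance is a common rater tendency C, and that the constructs are otherwise unrelated:

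X = √m·C + √(1−m)·E₁ and Y = √m·C + √(1−m)·E₂, with C, E₁ and E₂ independent and of unit variance.

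Then Var(X) = Var(Y) = m + (1−m) = 1 and Cov(X, Y) = √m·√m = m, so the correlation is m. Hence m = 0.2 gives 0.2 and m = 0.4 gives 0.4. For a scale scored in the unfavourable direction, such as complexity, the sign reverses and the size is the same.

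**3. Illustration at the pilot sites**

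Table 3 sets a minimum team of 2 + 2 + 1 = 5, so three sites give at least 3 × 5 = 15 raters. The table shows 20,000 simulated data sets per row, with a two-sided 5% Pearson test and no true link:

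| m (assumed) | mean r | false-positive rate |
|---|---|---|
| 0 | 0.00 | 5.1% |
| 0.2 | 0.20 | 11.1% |
| 0.3 | 0.29 | 19.3% |
| 0.4 | 0.39 | 32.6% |

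More raters do not help: with 60 separate raters and m = 0.3 the rate is 65.4%. If the outcome comes from a source without the rater tendency, n = 15 gives a mean r of about 0 and a rate of 4.9% to 5.1% for m = 0.2, 0.3 and 0.5. The continuous scores, the test and m are assumptions; the plan names logistic regression. The rates show a direction and a range, not an estimate.

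**4. Methods against Table 6**

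The Methods paragraph counts clinical effectiveness among the outcomes on which barriers may act. Neither row 3 of Table 6 nor the Aim 1 analysis paragraph includes it.

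**5. What a site-level comparison can show**

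With n = 3 sites the critical |r| at the two-sided 5% level is 0.997, so any comparison of delivery measures across the pilot sites is descriptive.

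**The case against.** The strongest reply is that this is a declared and reasoned choice. The protocol says openly that the three scales are perceptions, chosen for their salience to stakeholders and as early indicators. The raters must have managed treated patients, and at pilot sites they answer a year after training, so their views rest on experience. Question 3 also draws on interviews, in a mixed-methods design. This stands as a reason to keep FIM, AIM and IAM, and replacing them as the definition of success would be a debatable trade. It does not separate rater tendency from a real link. The interviews are held with the same team, so they are not an independent measure of delivery.

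A reader might infer more than the documents support:

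- *That all of question 3 is affected equally.* Capacity comes from another instrument at another time.
- *That a site with high feasibility ratings and many interruptions would be classed as a success.* No rule classes sites, and interruptions are used elsewhere to judge training.
- *That the Roadmap rests on this correlation.* Aim 3 compiles the results of Aims 1 and 2, including clinical and process data.
- *That Table 2 makes the analysis circular by filing FIM, AIM and IAM under intervention characteristics.* That column tags data sources and does not set analytic roles; disease outcomes carry the same tag. In the Aim 1 analysis the three scales appear only as outcomes.
- *That ORIC's tag would shift hospital problems onto the drug.* Readiness is analysed under its own name, so this is a labelling conflict only.

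It is also fair to say that the size in step 2 follows directly from the assumed share.

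**Conclusion.** The point holds in a limited form. As mapped, the scored answer to question 3 relates the implementation team's perceptions of readiness, climate and complexity to the same team's perceptions of feasibility, acceptability and appropriateness. Part of any association can be shared rater tendency. How large a part is unknown: a spurious correlation of about 0.2 to 0.4 requires a shared variance of 0.2 to 0.4 in both scores, which is an assumption. The inclusion of clinical effectiveness in the Methods is not carried through to this question, although relevant data are collected. The conflict over ORIC's domain is real but minor, and separate.

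**What to change.** 1. In row 3 of Table 6 and in the Aim 1 analysis paragraph, keep FIM, AIM and IAM, and describe their correlation with ORIC, ICS and complexity as a correlation among perceptions.
2. In the same two places, add delivery measures the study already collects: infusion-issue interruptions from the interruption record, duration of each cycle, proportion of patients enrolled, and the disease outcomes listed under clinical effectiveness. Report them descriptively per site, beside the readiness, capacity and complexity scores. This also brings question 3 into line with the Methods paragraph.
3. Separately, reconcile ORIC's domain in Table 2 with the Phase 2 section.

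**Cost.** The change is to wording, plus a little more analysis work; no new data are needed. Days from training to first infusion is not proposed, because the article does not list it as a data item. The limitation is that, with three pilot sites, the added comparison can only be descriptive.
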